## Abstract

### *Background*

Single plate osteosynthesis is commonly employed when performing surgical stabilization of midshaft clavicle fractures. In recent years, a smaller structural low-profile double plating technique has been described as a possible solution for the high removal rates associated with single plating. A previous meta-analysis has demonstrated that low-profile double plating attains the same healing rates as single plating without a higher chance of fracture-related infections. This meta-analysis, however, was based on relatively small studies. Therefore, a multicentre prospective natural experiment was designed using natural variation in treatment regimens and geographical location of the trauma as treatment allocation mechanism to compare both treatments on a larger scale. This manuscript describes its protocol.

### *Material & Methods*

Patients ( $\geq 18$  years) with primary midshaft clavicle fractures that are eligible for operative treatment will be included. Treatment allocation will be determined by the geographical location of the accident and local hospital providing treatment. In two centres, single plating is the treatment of choice for these patients. In two others, low-profile double plating has become the standard treatment. For the low-profile double plating group, one superiorly positioned VariAx 2.0mm and one anterior VariAx 2.4mm or 2.7mm plate will be used. For the single plating group, the standard locally available implant will be used. A total of 336 patients will be included. The primary outcome of interest is re-intervention. Secondary outcomes include complications, operative time, length of incision, functional scores (DASH, EQ-5D-DL, VAS-Pain/Satisfaction) and cost-effectiveness.

### *Discussion*

This study will determine whether low-profile double plating has significant clinical and cost-effective benefits over single plating techniques in midshaft clavicle fractures. The study will also give insight in the performance of a natural experiment study design for orthopedic trauma research.

26

## 27 **Trial registration**

28 This study has been registered on ClincialTrials.gov, identifier NCT 05579873.

## 29 **Keywords**

30 Clavicle injuries, Bone Plates, Non-randomized Controlled Trials as Topic, Natural Experiments

31

## 32 **Background**

33 Exposed to the exterior environment due to a lack of surrounding muscles or subcutaneous tissue, the  
34 clavicle is prone to traumatic injury. Clavicle fractures account for 5 to 6% of all fractures, of which  
35 69 to 81% occur in the midshaft. [1,2] Surgical stabilization using a single plate, positioned either  
36 anteriorly or superiorly, is the most common surgical technique when patients/surgeons decide on  
37 operative treatment. [3] The major disadvantage of plate fixation, however, is implant irritation. As a  
38 result, up to 64% of patients undergo re-interventional surgery for implant removal. [4]

39

40 In recent years a low-profile double plating technique with smaller plates has been described as a  
41 possible solution to reduce the high rates of implant irritation. [5] Biomechanically, low-profile dou-  
42 ble plating is expected to be at least as stable as single plating. [6] A recently published meta-analysis  
43 showed that low-profile double plating for midshaft clavicle fractures is a safe procedure attaining  
44 the same high union rates seen in patients treated with single plating. [7] Additionally, double plating  
45 appears to have a lower overall complication and reintervention rate, mainly due to the lower  
46 incidence of implant-related complaints. Low-profile dual plating, however, is a relatively new  
47 technique and should be further explored to test whether our findings can be confirmed.

48

Although randomized controlled trials (RCTs) are considered the gold standard for testing the effectiveness of such new interventions, the artificial conditions that are usually imposed on surgical practice frequently limit the feasibility and the generalizability of its results. A natural experiment (NE) design offers a possible solution. NEs are observational studies in which patients are exposed to either the experimental or the control condition, and treatment allocation is determined by factors outside the control of the investigators (e.g., geographical location). [8] Although not the same, the process governing treatment allocation arguably resembles that of randomization, since treatment allocation is expected to be (to a large extent) independent of patients' characteristics and their prognosis.

This protocol encompasses a prospective NE comparing low-profile double plating to single plating in midshaft clavicle fractures. The primary endpoint is the overall re-intervention rate, with a specific interest in implant removal due to irritation. Secondary endpoints include all complications, healing, the general quality of life, functional results, and cost-effectiveness.

## **Methods/Design**

### **Aim**

To compare single plating to low-profile double plating in midshaft clavicle fractures with regard to re-intervention, complications, healing, quality of life, functional results, and cost-effectiveness.

### **Study design**

This study will be a multicenter prospective cohort study between four Swiss centers with comparable patient case-mix. At which hospital/surgeon trauma patients are presented after an accident depends on the geographical location of the accident. We hypothesize that different Swiss centers treat a similar caseload of trauma patients with clavicle fracture and that the patient case-mix is similar across the different centers.

73 Of the four participating centers, two centers are specialized in single plating, and two are specialised  
74 in low-profile double plating will participate. Treatments will be naturally allocated by the geograph-  
75 ical location of the accident. Although centers are divided into either category based on their standard  
76 treatment of care, surgeons will be allowed to alter their treatment plan based on their own surgical  
77 expertise and according to what they (after consultation of the patient) consider the most appropriate  
78 treatment. This study design is sometimes referred to as a NE and is arguably less prone to confound-  
79 ing bias than conventional observational studies, provided the above-mentioned assumptions hold.

[figure not shown]

**Figure 1** Schedule of enrolment, interventions, and assessments

## Participant selection

## 84 Eligibility criteria

85 All adult patients (>18 older) presenting at the emergency department (ED) or outpatient clinic with  
86 midshaft clavicle fractures (Robinson Type II or AO/OTA 15.2) [9] will be included. In-and exclu-  
87 sion criteria are shown in Figure 2. Patients will be screened for eligibility by the treating physician  
88 at presentation to the emergency department or during outpatient visits (within two weeks after  
89 trauma).

### INCLUSION CRITERIA

- Aged 18 years or older.
- Written informed consent.
- Primary midshaft clavicle fracture (Robinson Type II or AO 15.2).
- Patients that are eligible for operative treatment of clavicle fracture, which may include but is not limited by:
  - Displacement of one or more shaft width.
  - Shortening of more than 1cm in length.
  - High physical activity level.

### EXCLUSION CRITERIA

- Delayed presentation (>14 days).
- Initial operative treatment at a non-participating hospital.
- Open fractures.
- Pathological fractures.
- Re-fractures of the clavicle.
- Cognitive impairment or language barrier precluding answering questionnaires.
- Unable to complete follow-up (e.g. different residential area/tourist).

90

91 **Figure 2** In/Exclusion criteria

92

93

94

95 *Participant recruitment and screening*

96 Patients will be asked to participate in the study after the established decision on operative treatment.  
97 If eligible, the treating physician or local investigator will explain to each participant the nature of  
98 the study, its purpose, the procedures involved, the expected duration, the potential risks and benefits,  
99 and any discomfort it may entail. Each participant will be informed that participation in the study is  
100 voluntary, that he or she may withdraw from the study at any time, and that withdrawal of consent  
101 will not affect his or her subsequent medical assistance and treatment. The participant will be in-  
102 formed that their pseudonymized medical records may be examined by authorized researchers other  
103 than their treating physician.

104 *Data management*

105 Data will be stored in pseudonymized form in an encrypted online database by the local investigators,  
106 which can access their respective individual patient data. Full access to the database is granted to the  
107 study coordinator.

108 **Study interventions**

109 *Low-profile double plating group*

110 Low-profile double plating consists of one Stryker VariAx 2.0mm plate positioned on the superior  
111 aspect of the clavicle and a second Stryker VariAx 2.4mm or 2.7mm on the anterior side. Use of this  
112 implant will be according to the manufacturer's indication of use.

113

114 *Single plating group*

115 The choice of implant used for single plating is left at the discretion of the treating surgeon and the  
116 availability of implants in participating centers. Possible implants consist of 2.7 and 3.5mm plates  
117 placed on the superior or anterior side.

118

## Standardization of care

Preoperative care will consist of general anesthesia and routine antibiotic prophylaxis. Incision and cutaneous nerve sparing are left at the treating surgeon's discretion and will be mentioned in the operation report. In case of a multi-fragmentary fracture pattern, bridge plating will be performed. In case of a simple fracture, a neutralization plate (with or without lag screws) or a compression plate will be used. Closure of deltopectoral fascia with absorbable braided sutures and skin with absorbable or nonabsorbable monofilament sutures will be performed for all patients. Operations will either be performed or directly supervised by a specialized trauma surgeon. Aftercare comprises a sling for comfort for 1-2 weeks, no weight bearing for six weeks, and outpatient clinic visits, including AP and axial clavicle X-rays at six weeks, three months, and one year after surgery in both treatment groups.

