### Secondary Objective

---

Re-intervention rate (including implant removal) after 1-year follow-up.

---

---

All other complications (including complications treated non-operatively)

- Fracture related infection.
- Symptomatic non-union defined as absence of radiological signs of healing (callus formation or fading of fractures lines) combined with pain at the fracture site at 9 months.
- Asymptomatic non-union defined as absence of radiological signs of healing (callus formation or fading of fracture lines) without any clinical symptoms.
- Numbness below scar line related postoperatively and at 12-months follow-up.
- Self-reported implant irritation or other reasons for implant removal at 12 months.

Operative time.

Length of surgical incision.

QuickDASH score at baseline (pre-injury), 3- and 12-months follow-up.

EQ-5D-5L at baseline (pre-injury), 3- and 12-months follow-up.

VAS pain and patient satisfaction at 3- and 12-months follow-up.

---

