**Table 1: Primary and secondary outcomes.**

**The outcome measure, follow-up and timeline**

At baseline, the treating physician or local investigator will collect the following characteristics: age, gender, body mass index (BMI), smoking status, comorbidities, medication, trauma mechanism, concomitant injuries and planned operative procedure (including treating hospital and surgeon), pre-injury DASH and EQ-5D-5L. The x-ray at presentation or outpatient clinic visit will be used to determine fracture type and dislocation. Fracture type will be determined according to the AO/OTA classification system for midshaft clavicle fractures. [9] Patients will receive the operation within two weeks of presentation.

The patients will return to the outpatient clinic at three and twelve months. The outpatient clinic visit will include several questionnaires (e.g., VAS, EQ5D, DASH), x-rays, and a physical examination (Table 2). All data and adverse events (AE) will be registered. At two years, the patient will be either

seen at the outpatient clinic visit or interviewed by telephone, and the electronic patient database will be accessed to assess patient-reported outcome measures (PROMS), complications and reintervention rate.

All the measurements and examinations described are part of standard care, except the questionnaires. The questionnaires will be filled in at regular outpatient clinic visits or by telephone interview.

|                            | Baseline (at inclusion) | 12-weeks follow-up | 12-months follow-up | 24-months follow-up |
|----------------------------|-------------------------|--------------------|---------------------|---------------------|
| Re-intervention            |                         |                    | X                   | X                   |
| X-ray                      | X                       | X                  | X                   |                     |
| DASH*                      | X                       | X                  | X                   |                     |
| EQ5D-5L*                   | X                       | X                  | X                   |                     |
| VAS pain and satisfaction* | X                       | X                  | X                   |                     |
| Complications              |                         | X                  | X                   | X                   |

\* Not part of standard care.

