## **Statistical analysis.**

The statistical package IBM SPSS Statistics for Windows, version 28.0, will be used for analysis. Depending on the normality distribution, baseline characteristics will be described as means and standard deviations or median and interquartile range for continuous variables. Categorical variables will be reported in counts and percentages. Differences between treatment groups will be analyzed with an independent samples student's T-test or Mann-Whitney-U test (depending on distribution). Categorical variables will be analyzed using the Chi-square test.

The primary outcome will be analyzed using logistic regression with revision surgery as the dependent and treatment as the independent variable. The relative risk (RR) will be calculated with a 95% confidence interval (95% CI). Multivariable logistics regression analysis will also be performed to account for potential known confounders including age and fracture type.

Missing data (caused by incomplete hospital documentation or loss-to-follow-up) will be addressed using multiple imputation techniques.

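### Operative time: the only group comparison stated for continuous variables is unadjusted, although technique largely follows hospital and operators may be specialists or supervised (minor)

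*Protocol*

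**What the plan says.** Table 1 of the protocol lists "Operative time" among the secondary outcomes, and the abstract does the same. Neither defines it.

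On who operates, the Standardization of care section says: "Operations will either be performed or directly supervised by a specialized trauma surgeon". It does not fix the share of each kind of operator, overall or by hospital.

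On allocation, the abstract says: "In two centres, single plating is the treatment of choice for these patients". The two other hospitals use double plating as standard. The Study design section lets surgeons depart from the local standard, so technique follows hospital largely but not completely.

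On data, the baseline list in the section on outcome measure, follow-up and timeline includes "concomitant injuries and planned operative procedure (including treating hospital and surgeon". No separate list of data from the operation is printed.

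On analysis, the Statistical analysis section first explains how baseline characteristics are described and then states: "Differences between treatment groups will be analyzed with an independent samples student's T-test or Mann-Whitney-U test (depending on distribution". Regression appears only for re-intervention: "The primary outcome will be analyzed using logistic regression with revision surgery as the dependent and treatment as the independent variable", followed by "Multivariable logistics regression analysis will also be performed to account for potential known confounders including age and fracture type".

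**The concern.** The natural-experiment argument is that the place of the accident makes patients similar across hospitals. It says nothing about the people who operate. Operator experience belongs to the hospital, and the hospital largely determines the technique. With two hospitals per technique, a difference in the share of supervised operations has little chance to average out. The same applies to operations in which another injury is treated in the same session, and to fracture pattern where surgeons depart from the local standard.

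Operative time is an outcome that these factors can plausibly change directly. If it is compared without adjustment, a gap in operator or case mix could create, hide or reverse an apparent difference between plates.

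**Working it through.** The protocol gives no figure for operative time, so there is nothing to reproduce. The check has two parts.

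**1. The text, set side by side**

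| Question | What the protocol gives |
|---|---|
| Is operative time an outcome? | Yes, secondary (abstract, Table 1) |
| May operators differ in experience? | Yes, specialist or directly supervised (Standardization of care) |
| Is the technique separable from the hospital? | Only in part: two hospitals per standard technique |
| Which comparison is stated for a continuous variable? | t-test or Mann-Whitney test only |
| For which outcome is adjustment stated? | Re-intervention only; age and fracture type are named |
| Which operator data are listed? | A baseline entry with hospital and surgeon |

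Fracture type, age and concomitant injuries are already collected, so part of an adjusted analysis needs no new data. The actual first operator and any same-session procedure are not listed.

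**2. How large a spurious difference could be (illustration)**

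Input from the protocol: 336 patients, taken as 336 / 2 = 168 per arm.

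Assumed inputs, none of them in the documents: SD of operative time 20 to 30 minutes; extra time for a supervised operator 10 to 20 minutes; difference between arms in supervised share 0.2 to 0.6; no true plate effect.

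Formulas:
- spurious difference b = (difference in supervised share) × (extra minutes)
- SE = SD × √(2/168), which is 2.18 minutes for SD 20 and 3.27 minutes for SD 30
- chance of a significant result at two-sided 5% ≈ Φ(b/SE − 1.96)

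| Extra minutes | Share difference | b (min) | SD 20 | SD 30 |
|---|---|---|---|---|
| 10 | 0.2 | 2 | 15% | 9% |
| 15 | 0.4 | 6 | 79% | 45% |
| 20 | 0.6 | 12 | over 99% | 96% |

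Worked line: b = 0.4 × 15 = 6; for SD 20, 6/2.18 = 2.75 and Φ(2.75 − 1.96) = Φ(0.79) ≈ 0.79. With 152 per arm, the number before allowance for loss to follow-up, the middle row becomes 74% and 41%.

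The nominal rate is 5%. The table shows only that the mechanism can matter at this sample size. The range from 9% to over 99% reflects the assumed inputs and is not an estimate for this trial. If the supervised share is equal in both arms, b is zero.

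**The case against.** Four objections carry weight.

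*The unadjusted test may not be meant for operative time.* The sentence follows the one on baseline characteristics, and the section never names operative time. A reader might infer that the protocol prescribes a crude comparison of operative time. The text does not go that far. It states no other method for a continuous variable, and a statistical analysis plan that is not at hand could add one. This limits the point but does not remove it, because the one method on paper is unadjusted and adjustment is tied expressly to the primary outcome.

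*The data may be recorded anyway.* A reader might infer that operator details will be lost. That is not supported. The list in question is a baseline list, where the actual operator could not appear, and it does include hospital, surgeon and concomitant injuries. Whether the word planned also governs the surgeon is open. An operation report exists. What stands is that the surgeon entered at baseline may be the supervisor or may not be the one who operates, and that a concomitant injury is not the same as a second procedure in the same session.

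*Nothing shows that teaching mix differs between hospitals.* Correct. The sentence on supervision is itself a standardisation measure that applies at every centre. A reader might also carry the problem over to the cost-effectiveness conclusion. The protocol lists no cost items, so that step is speculation.

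*Adjustment is an imperfect remedy.* Also correct. Two hospitals per technique cannot separate plate from hospital. If a technique's difficulty influences who operates, adjusting for grade may remove part of the effect of interest. The fix has to allow for both.

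**Conclusion.** The point holds as a minor one. In a non-randomised comparison with two hospitals per technique, an unadjusted test is a weak method for operative time, and it is the only method that the protocol states for a continuous variable. Differences in case or operator mix could pass for a plate effect. Their size and direction cannot be known from the protocol, and every figure above other than the sample size is assumed or follows from assumptions.

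The conclusion rests on two premises: that the stated t-test or Mann-Whitney test would be used for operative time if nothing else is specified, and that operator or case mix may differ between hospitals. The primary outcome and the sample size are not affected, and no contradiction or wrong figure is involved.

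**What to change.** - **Data.** From the existing operation report, record the actual first operator (specialist or supervised) and any other procedure done in the same session.
- **Definition.** Define operative time as skin-to-skin for the clavicle procedure.
- **Analysis.** In the Statistical analysis section, specify a linear model for operative time with technique, age, AO/OTA fracture type and same-session procedure. Report the adjusted mean difference with its 95% CI.
- **Second model.** Add operator grade in a separate model shown beside the first, because technique may influence who operates.
- **Interpretation.** State that, with two hospitals per technique, the result remains partly a comparison of hospitals.

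The cost is two extra data items per operation and one additional model. The fix does not change patient care, the primary analysis or the sample size.

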## Study outcomes

The primary outcome of this study is the number of re-interventions after two years of follow-up. Secondary outcomes include the number of re-interventions at one year of follow-up, all complications such as fracture-related infection [10], (a)symptomatic non-union, numbness below the scar, and self-reported implant irritations, disability of the shoulder and arm (DASH) score, EuroQol (EQ)-5D score, and the visual analogue scale (VAS) score for pain and patient satisfaction at 3, 12, and 24 months follow-up. A complete overview of the primary and secondary outcomes can be found in Table 1.

---

### Primary Objective

---

Re-intervention (all indications) after 2-year follow-up

---

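### The primary outcome is expected to be driven largely by implant removal, and technique largely follows hospital, so the planned analysis cannot separate the implant's effect from hospital removal practice.

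*Protocol*

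**What the plan says.** **Outcome.** Table 1 defines the primary outcome as "Re-intervention (all indications) after 2-year follow-up". The Background reports that "up to 64% of patients undergo re-interventional surgery for implant removal", says that double plating "appears to have a lower overall complication and reintervention rate, mainly due to the lower" frequency of implant-related complaints, and describes the primary endpoint as overall re-intervention "with a specific interest in implant removal due to irritation".

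**Allocation.** The abstract states: "Treatment allocation will be determined by the geographical location of the accident and local hospital providing treatment". Study design adds: "Of the four participating centers, two centers are specialized in single plating, and two are specialised" in low-profile double plating. Surgeons may depart from the centre's standard technique; how often is not stated. The comparability assumption in that section concerns caseload and patient case-mix.

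**Care and analysis.** Standardization of care covers anaesthesia, antibiotics, fixation principle, closure, aftercare and visits. It does not mention the decision to remove a plate. Statistical analysis gives a logistic model with treatment alone, then an adjusted model whose confounders include age and fracture type. Hospital and surgeon are recorded at baseline but appear in neither stated model.

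**Irritation data.** Table 1 lists, among the complications, self-reported implant irritation or other reasons for removal, at 12 months. Study outcomes also names self-reported irritation, in a sentence ending with 3, 12 and 24 months; it is unclear whether those times apply to irritation. Table 2 marks complications at 24 months without saying which.

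**The concern.** Re-intervention for irritation happens only when a patient has complaints and the patient and surgeon then decide to remove the plate. The implant can affect the first step. The second also depends on how readily a hospital removes plates. With two hospitals per technique, any difference between the pairs of hospitals in that second step falls almost entirely on the treatment contrast.

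Similar patients at every hospital would not help, because the problem arises after surgery and not from who is enrolled. Adjusting for age and fracture type would not help either. A hospital term would be of little use: technique is nearly a function of hospital, and only patients treated against their centre's standard would separate the two.

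At stake is the main conclusion. The Discussion says that the study will help show whether double plating has clinical and cost-effective benefits. A significant primary result, or a null one, could reflect removal practice as well as the implant.

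**Working it through.** **Inputs from the protocol.** Total 336 patients and 5% expected loss to follow-up: 336 / 2 × 0.95 = 159.6, so about 160 analysed per arm. Alpha is 0.05, taken as two-sided. (Inflating 152 per group for 5% loss gives 152 / 0.95 = 160, or 320 in total and not 336. That is a separate matter, and the result below barely depends on it.) The protocol gives no control rate and no removal rate by centre, so its figures cannot show how large this bias is.

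**Assumed inputs.** Irritation in 20% or 30% of both arms, other re-operations in 4%, and a removal share (the proportion of irritated patients whose plate is removed) of 60%, 40% or 30%. None of these is in the documents.

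**Step 1: re-intervention rate = 0.04 + irritation × removal share, with no technique effect.**

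| Irritation, both arms | Removal share, single v double | Single | Double | Difference |
|---|---|---|---|---|
| 20% | 60% v 40% | 0.04 + 0.20 × 0.60 = 16% | 0.04 + 0.20 × 0.40 = 12% | 4 points |
| 20% | 60% v 30% | 16% | 0.04 + 0.20 × 0.30 = 10% | 6 points |
| 30% | 60% v 30% | 0.04 + 0.30 × 0.60 = 22% | 0.04 + 0.30 × 0.30 = 13% | 9 points |

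**Step 2: chance of a significant result.** Pooled two-proportion test with n = 160 per arm. For 16% v 10%:

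- Standard error under the null: √(2 × 0.13 × 0.87 / 160) = 0.0376.
- Standard error under the alternative: √((0.16 × 0.84 + 0.10 × 0.90) / 160) = 0.0375.
- Probability: Φ((0.06 − 1.96 × 0.0376) / 0.0375) = Φ(−0.37) = 0.36.

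| Comparison | 152 per arm | 160 per arm | 168 per arm |
|---|---|---|---|
| 16% v 12% | 0.171 | 0.177 | 0.184 |
| 16% v 10% | 0.342 | 0.357 | 0.372 |
| 22% v 13% | 0.542 | 0.563 | 0.584 |

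With no technique effect and equal practice this would be 0.05.

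**Step 3: the primary outcome cannot tell the explanations apart.**

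- Same implant, different practice: irritation 20% in both arms, removal share 60% v 30%, gives 16% v 10%.
- Better implant, same practice: irritation 20% v 10%, removal share 60% in both, gives 0.04 + 0.20 × 0.60 = 16% v 0.04 + 0.10 × 0.60 = 10%. The result is identical.
- Better implant, opposite practice: irritation 20% v 10%, removal share 30% v 60%, gives 0.04 + 0.20 × 0.30 = 10% v 0.04 + 0.10 × 0.60 = 10%. The benefit disappears.

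**Step 4: no systematic direction.** Suppose that re-intervention rates vary at random between hospitals, with no technique effect and two hospitals of 76 patients per arm. In simulation the two-sided false-positive rate is 7% with a between-hospital standard deviation of 2 points and 17% with 5 points, at a mean rate of 25%. At a mean rate of 15% it is 8% and 22%. About half of these errors favour each technique.

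**The case against.** **All-indication re-intervention is a legitimate pragmatic endpoint.** This stands, and the endpoint should be kept. The difficulty lies in attributing a difference to the implant.

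**The protocol already collects irritation and reasons for removal.** This largely stands. A reader might infer that the plan has nothing on the subject; Table 1, Study outcomes and Table 2 show otherwise. The gap is narrower: the one item that names removal reasons is fixed at 12 months, the timing elsewhere is unclear, and nothing connects it to the 24-month primary outcome.

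**Breakdowns by indication belong in a SAP, which is not shown.** This stands in part, and the confounder list is open-ended. But a SAP cannot recover indications or irritation status that were not collected to 24 months.

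**The size is assumed.** This stands. A twofold gap in removal share gives 36%; the milder gap gives 18%. Neither shows that bias is likely in these four hospitals.

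**Irritation is not a clean measure either.** This stands. It is self-reported by patients who are not described as blinded, and it is tied to the same hospitals. A hospital that removes readily may also record irritation more often, and removal ends further exposure to the plate.

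**Conclusion.** The point holds as one about attribution. Under the stated models, a difference in hospital removal practice could create, hide or reverse an apparent benefit of double plating, and the planned data would not reliably show which had happened. It rests on three features of the protocol: an outcome expected to be driven largely by removal, technique that largely follows two hospitals per arm, and no common basis for the removal decision. The false-positive rates of 18% to 56% are scenarios resting on assumed irritation and removal shares.

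Two stronger readings are tempting and not supported. One is that removal practice will be reported as a benefit of double plating. That would require the single-plate hospitals to remove more readily, and the documents describe no centre's practice. The other is that technique and hospital coincide completely. Surgeons may depart from the centre standard, so the overlap is close but not total.

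The matter should be corrected while the data can still be collected. It does not invalidate the primary outcome.

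**What to change.** Keep the primary outcome and add the following to the protocol. No clinical rule for removal is proposed.

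1. Record the date and indication of every re-intervention to 24 months: irritation, patient request or routine, infection, non-union, implant failure, other.
2. Record irritation at 24 months whether or not the plate was removed, and align Table 1, Table 2 and Study outcomes on this.
3. Pre-specify two analyses beside the primary: (a) re-intervention excluding all implant removals for irritation, request or routine; (b) irritation by 24 months regardless of removal. In the same-implant scenario above these would be 4% v 4% and 20% v 20%, against 16% v 10% for the primary. Analysis (a) must exclude removals for irritation too; otherwise it still depends on the removal threshold.
4. Tabulate by hospital the share of irritated patients whose plate was removed, and re-interventions split into removal and non-removal.
5. State how the results will be read. Analysis (b) depends less on the removal threshold, but it is still unblinded self-report from the same hospitals, so it supports attribution to the implant without proving it. A primary difference with no accompanying difference in (a) or (b) should not be attributed to the implant.

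The cost is a few data items at a 24-month contact and record review that are already planned, one extra table, and a more cautious conclusion.
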